#### Data analysis

All statistical analyses will be conducted using SPSS 21 (IBM Corp., Armonk, NY, USA). Generalised linear models, estimating variance appropriately for repeated measures, will be used to determine whether there are differences among the Acticoat™ group, the Acticoat™ combined with Mepitel™ group and the Mepilex Ag™ group in primary and secondary outcomes. Changes in the intervention effects will be examined with burn depth, burn total body surface area, mechanism of injury, anatomical location of the burn, skin type, ease of dressing removal and application and physical function considered a priori to be of potential interest. All data will be analysed as intention to treat and on a per protocol basis, with the intention to treat analysis being the primary approach for this trial. Any missing data will be handled using the multiple imputation method. All tests will be two-tailed and only those with a *p* value <0.05 will be considered statistically significant.

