The standard of care in burn dressings for small to medium partial thickness burns has changed in the last 10–15 years. Currently silver-depositing fabric and foam dressings are the gold standard used to manage the bio-burden of a wound, with or without a silicone skin interface [13]. Acticoat™ (Smith & Nephew, Hull, UK) has been available since the 1990s and is the most widely used silver dressing in the developed world. It needs to be moistened with sterile water to promote the release of silver onto the burn wound and can be left on for 3–4 days. Acticoat™ may be used alone or in combination with a Mepitel™ dressing (Mölnlycke Healthcare, Mikkeli, Finland), which acts as a non-stick interface between Acticoat™ and the burn wound. Mepitel™ is a silicone-coated nylon grid product that utilises non-stick Safetac™ technology to reduce the pain and trauma experienced by children during dressing changes and the amount of silver in direct contact with the wound. Mepilex Ag™ (Mölnlycke Healthcare, Mikkeli, Finland) has been available since 2007 and is a soft foam, silver-impregnated dressing that absorbs exudate and maintains a moist wound environment [14]. Silver particles are released from Mepilex Ag™ when it is moistened from direct contact with wound exudate. It also has a silicone Safetac™ interface layer incorporated within its design that, in a similar way to the Mepitel™, serves to promote easy removal of the dressing and reduce pain and trauma during dressing changes [14].

Many trials have been conducted regarding the efficacy of silver dressings for treating burn injuries, using topical silver sulfadiazine applications as the control or comparator dressing. However, these silver sulfadiazine applications have been shown to delay re-epithelialisation and are painful to apply and remove, indicating the possibility of bias in the results of these trials [13,15,16]. Additionally, despite the large number of silver-impregnated burn dressings that have become available on the market, very few high-level trials have been conducted that compare these dressings in paediatric or adult patients. For paediatric patients in particular, identifying silver dressings that are associated with lower levels of pain, require fewer reapplications and promote a fast rate of re-epithelialisation is vital.

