### Study design

This study is a prospective, randomised controlled trial. Participants will be randomised to receive one of three commonly used dressings for burn wounds, (1) Acticoat™, (2) Acticoat™ and Mepitel™ combined or (3) Mepilex Ag™, in order to determine the effects of the dressings on pain and the rate of re-epithelialisation in acute, partial thickness burns in children. It is hypothesised that silver dressings with a silicone interface, compared to no silicone interface, will decrease the time to re-epithelialisation of a burn injury and decrease the amount of pain and distress experienced during dressing changes within a paediatric population. The design of data collection is displayed in Figure 1.

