### Data collection

Demographic information and clinical details will be obtained from the caregiver and the patient’s chart regarding the mechanism of the burn injury, site of the injury, total body surface area of the burn and first aid the patient received. Children over the age of 4 years will be given the Ditto™ (virtual reality) device (Diversionary Therapy Technologies, Queensland, Australia) to engage in the “Bobby got a Burn” procedural preparation story at their first dressing change. These children may also engage in a choice of games or stories on the Ditto™ during all dressing changes. At the first dressing change only, each participant will have their burn/s scanned using the LDI2-BI (VR) Laser Doppler Imager (LDI) (Moor Instruments, Axminster, Devon, UK), which measures wound depths (in blood perfusion units) as a percentage of total wound area. The laser Doppler imager scan will provide an objective assessment of burn depth to enable a comparison of treatment group demographics [19]. Participants who have burn wounds on different body parts will have separate scans completed for each body part involved. If burn wounds are circumferential or across curved areas, more than one scan will be taken at the frontal, lateral and medial aspects to obtain an accurate scan. In addition, blinded photo reviews of burn depth will be undertaken by a panel of burn specialists (consultants and nurses).

At each dressing change appointment, pain, behaviour and physiological measures (pulse rate and respiratory rate) will be taken before and after dressing removal and before and after the re-application of a new dressing. The time taken for the dressing removal, cleaning and re-application procedure, the number of nurses required to complete the entire procedure, quantity of dressings used and analgesia given to the participant will be recorded. A tracing of the wound using Visitrak™ grids (Smith & Nephew, Hull, UK) and a photograph using the 3D LifeViz Camera (Quantificare, Cedex, France) will be taken. Nursing staff treating the child will be surveyed on a 5-point Likert scale regarding the ease of use of the dressing for that particular child. Parents or caregivers and children over the age of 8 years will be surveyed on a 5-point Likert scale regarding their physical function while wearing the dressing.

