### Secondary outcome measures

#### Physical function

A self-report of the participants’ ease of movement while wearing the dressing will be obtained using a 5-point Likert scale question from children over the age of 8 years or their caregiver at the first dressing change [26].

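### Two of the factors chosen to examine changes in the treatment effect, ease of dressing removal and application and physical function, are measured after randomisation on the allocated dressing

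*Protocol article*

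**What the plan says.** In the protocol article, the Data analysis section first states that generalised linear models will compare the three dressing groups on primary and secondary outcomes. A separate sentence follows: "Changes in the intervention effects will be examined with burn depth, burn total body surface area, mechanism of injury". That list continues with anatomical location and skin type, and closes with "ease of dressing removal and application and physical function considered a priori to be of potential interest". Intention to treat is named as the primary approach.

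Other sections show when the last two factors are recorded:

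- **Ease of use.** Under Data collection, the nurses treating the child, at each dressing change, "will be surveyed on a 5-point Likert scale regarding the ease of use of the dressing for that particular child".
- **Physical function.** Under the heading "Secondary outcome measures", a self-report of "ease of movement while wearing the dressing will be obtained using a 5-point Likert scale question", taken at the first dressing change from children over 8 years or their caregiver.

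The Background says that the silicone layer of one study dressing, like the separate silicone product used in another arm, "serves to promote easy removal of the dressing and reduce pain and trauma during dressing changes". The Study design section hypothesises that "silver dressings with a silicone interface, compared to no silicone interface, will decrease the time to re-epithelialisation of a burn injury", and that pain and distress during dressing changes will also fall.

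**The concern.** A factor used to ask whether a treatment effect differs between patients should be fixed before treatment starts. Randomisation balances the arms on such factors, so the comparison within each level is still a fair one. Neither of these two factors meets that condition. Each describes how the allocated dressing behaves on the child, so each can differ between arms because of the treatment.

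The sentence can be read in two ways, and both give trouble. If the factors enter as covariates, the model estimates the effect that remains once ease of handling or movement is held equal, which is not the effect of using the dressing. If they enter as interactions or subgroups, children with the same rating on different dressings are compared, and those children need not be alike in other respects. At stake is a pre-specified analysis that could make a dressing that works through easier removal look as if it did little, or that could report an effect modifier with no causal meaning.

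**Working it through.** **1. Timing of the seven listed factors**

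| Factor | What the protocol article says | Fixed before the first study dressing? |
|---|---|---|
| Total body surface area, mechanism, location | Obtained from caregiver and chart (Data collection) | Yes |
| Skin type | Patient characteristic; source not stated | Yes, by nature |
| Burn depth | Laser Doppler: "At the first dressing change only, each participant will have their burn/s scanned"; also a blinded photo review. The source used for this analysis is not named | Depends on the source |
| Ease of removal and application | Nurse rating at each dressing change | No |
| Physical function | Rated while the dressing is worn, at the first dressing change (Physical function) or at each change (Data collection) | No, on either schedule |

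**2. Place on the causal path, by the document's own account**

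- Dressing to ease of removal to pain: the Background sentence on the silicone layer.
- Pain and distress to slower healing: Background and Discussion.
- Ease of removal therefore lies on the stated path to pain, and by one further step on the path to healing.
- Physical function is not placed on the path to healing anywhere. The case against it as a covariate or modifier is that it is measured on the allocated dressing and is itself an outcome to be compared by arm.

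**3. The plan's own figure**

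Inputs from the Sample size section: difference 3 days, SD 4 days, 80% power, α 0.05; two-tailed from Data analysis.

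n per group = 2 × (1.960 + 0.842)² × 4² / 3² = 2 × 7.85 × 16 / 9 = 27.9, so 28. Power at 28 per group is 0.801. The stated figure is reproduced, and it involves no covariate.

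**4. Used as a covariate: mediated share**

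The share p of the effect that passes through the variable is not in the document, so it is varied. Adjusted effect = 3 × (1 − p) days.

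| p | Adjusted effect (days) | Simulated (days) |
|---|---|---|
| 0% | 3.00 | 3.04 |
| 25% | 2.25 | 2.26 |
| 50% | 1.50 | 1.52 |
| 75% | 0.75 | 0.73 |
| 100% | 0.00 | 0.01 |

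The simulation used two arms of 28, SD 4, a true reduction of 3 days, a dressing that shifts the variable by 1 SD (assumed), and 4,000 runs per row. Without the variable in the model, the estimated reduction stayed between 2.99 and 3.03 days in every row.

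**5. Conditioning when the variable shares a cause with healing**

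Suppose an unmeasured patient or wound feature U correlates 0.5 with the rating within arm and shortens healing by 2 days per SD (both assumed). The dressing again shifts the rating by 1 SD. Among children with the same rating, those on the easier dressing have U lower by 0.5 × 1 = 0.5 SD. That imbalance alone lengthens their healing by 0.5 × 2 = 1 day.

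- No mediation: 3 − 1 = 2.0 days (simulated 2.01).
- Half mediated: 1.5 − 1 = 0.5 days (simulated 0.50).

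The same imbalance arises within strata formed on the rating, so it applies to the subgroup reading as well as the covariate reading.

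**The case against.** The strongest defence is that the main comparison is untouched. Data analysis has one sentence for the group comparison and another for changes in the effect, and nothing says that the primary intention-to-treat estimate is adjusted for either variable. This stands. A reader might infer that the trial's primary result would be diluted, or that its power would fall well below 80%. The document does not support that, because it specifies no such adjusted primary test.

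A second defence is that the sentence may intend a mechanism analysis, with model detail left to an analysis plan. That is possible, but the article does not label it so, and it puts the two variables in one list with patient and burn characteristics. The point rests on what the text names, not on detail it omits.

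A third is that the numbers are assumed. This also stands: the mediated share, the 1 SD shift and the shared cause have no source in the document. The link from easy removal to healing runs through pain, so a calculation in days is one step removed from what the Background states.

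Two further criticisms may be tempting, and neither holds as an error. Laser Doppler depth is taken after the first dressing has been worn, but its stated purpose is to compare the groups descriptively, and a blinded photo review accompanies it. Age and time from injury are absent from the list, but the choice of covariates can be left to the analysis plan.

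**Conclusion.** The point holds for the analyses of changes in the intervention effect and for any model that contains either variable. Both variables are measured after randomisation on the allocated dressing. One is a listed secondary outcome, and the other is the document's own explanation for lower pain. Estimates conditional on them have no straightforward causal reading.

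The size of the bias cannot be computed from the document. The results above (2.25 to 1.5 days in place of 3 for a 25 to 50% mediated share, and 2.0 days with no mediation but an assumed shared cause) show direction and plausible scale only. The primary intention-to-treat comparison, the 28 per group and the 80% power are not shown to be affected. This is a correction to a pre-specified supporting analysis, worth making because it is easy, and not a fault in the trial's main test.

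**What to change.** In the Data analysis section:

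- Delete ease of dressing removal and application, and physical function, from the list of factors for examining changes in the intervention effect.
- Analyse both as outcomes compared by arm. If the mechanism is of interest, add an analysis explicitly labelled as exploratory mediation, with its assumptions stated.
- Restrict the modifier list to characteristics fixed before the first study dressing, such as total body surface area, mechanism, anatomical location and skin type.
- Use burn depth as a modifier only if it comes from an assessment made before that dressing. The article does not show that a superficial-versus-deep category is recorded at eligibility, so this should be confirmed first.

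The cost is a small wording change and the loss of two analyses that have no causal reading. Sample size and stated power do not change.

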**Methods/Design:**

Children aged 0 to 15 years with an acute partial thickness (superficial partial to deep partial thickness inclusive) burn injury and a burn total body surface area of ≤10% will be eligible for the trial. Patients will be randomised to one of the three dressing groups: (1) Acticoat™ or (2) Acticoat™ combined with Mepitel™ or (3) Mepilex Ag™. A minimum of 28 participants will be recruited for each treatment group. Primary measures of pain, distress and healing will be repeated at each dressing change until complete wound re-epithelialisation occurs or skin grafting is required. Additional data collected will include infection status at each dressing change, physical function, scar outcome and scar management requirements, cost effectiveness of each dressing and staff perspectives of the dressings.

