### Intervention

The intervention will be one of the Acticoat™, Acticoat™ combined with Mepitel™ or Mepilex Ag™ dressing arms that the participant is randomised into on presentation. This dressing will then be used to treat the burn wound and will be replaced every 3–4 days at each dressing change until re-epithelialisation occurs or grafting is required. The dressings will be applied according to the manufacturer’s instructions.

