#### Grafting

A note will be recorded if a participant’s wound requires grafting. Data collection will cease on that date for the participant as different dressings are used for wounds that are grafted; however all data preceding that point will be included for analysis.

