### Statistics

#### Sample size

The primary outcome measure will be days until wound re-epithelialisation. Previous data in paediatric burn patients demonstrated re-epithelialisation within 15 (SD = 4) days and a minimally clinically important difference is 3 days [6]. Thus sample size was calculated at 28 per group at 80% power with an α of 0.05. Allowing for 20% loss to follow-up, a total of 100 participants will be required. The burn centre treats 800 children per year with burns so recruitment for this study should be achievable within 1 year. This sample size will also be adequate to find a significant difference in data collected from pain scores, powered on data from a previous study [6].

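### As written, the rule to multiply impute any missing data gives grafted and stopped children a healing day that was never observed, which biases days to re-epithelialisation

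*Protocol article*

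**What the plan says.** The Sample size section of the protocol article names the outcome, "The primary outcome measure will be days until wound re-epithelialisation", and sizes the trial on a mean: "re-epithelialisation within 15 (SD = 4) days and a minimally clinically important difference is 3 days". The Data analysis section assigns primary and secondary outcomes to generalised linear models, makes intention to treat the primary approach, and closes the missing-data question in one sentence: "Any missing data will be handled using the multiple imputation method".

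Three other sections say when a child stops contributing data. Under Exclusion criteria, children who need a graft, contract an infection or change dressing type have data collected only up to that point. The Grafting section explains that "different dressings are used for wounds that are grafted; however all data preceding that point will be included for analysis". Discontinuation/adverse events says the same for infection and for a consultant's decision to change the dressing.

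The Intervention section sets the ordinary end of follow-up. The dressing "will be replaced every 3–4 days at each dressing change until re-epithelialisation occurs or grafting is required".

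**The concern.** Each rule is reasonable alone; the trouble is how they combine. A child who is grafted, infected or switched stays in the intention-to-treat comparison but has no recorded healing day. The only instruction for an absent value is multiple imputation, with no exception for these children.

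For a grafted child the day is not a value that someone failed to record. Healing under the assigned dressing did not happen, and grafting took its place, so it is a competing event. Grafting is also linked to slow healing, so the absence depends on the outcome itself and missing at random is not a credible assumption. Imputed days will tend to be too early. If more children are stopped in the slower arm, a true difference shrinks. If arms heal equally but graft unequally, a difference appears where there is none.

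**Working it through.** **The plan's own figure.** Inputs from Sample size: SD 4, difference 3 days, 80% power, α 0.05; Data analysis makes tests two-sided ("All tests will be two-tailed"). For two means, n = 2(1.960 + 0.842)² × 4²/3² = 27.9, so 28 per group, as stated (power 80.1%). This calculation takes the healing day as observed in every child analysed.

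**Assumptions for the bias.** The article gives no grafting or dressing-change rate and no stop day. Assume healing days are normal with SD 4, a share g of children still unhealed on day C are stopped on that day, and imputation uses treatment arm alone. The arm mean after imputation is then the mean of the children whose healing was observed. With z = (C − μ)/4 and p = P(Z > z):

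mean after imputation = μ − g × 4 × φ(z)/(1 − g × p)

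For C = 21:
- μ = 12: z = 2.25, φ = 0.0317, p = 0.0122
- μ = 15: z = 1.50, φ = 0.1295, p = 0.0668
- μ = 18: z = 0.75, φ = 0.3011, p = 0.2266

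Example with g = 1: the 15-day arm becomes 15 − 0.518/0.9332 = 14.44, and the 18-day arm becomes 18 − 1.2045/0.7734 = 16.44. The true difference of 3.0 days is estimated as 2.0.

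| Share g stopped | 15 v 18 days: stopped | Estimate | 12 v 15 days: stopped | Estimate |
|---|---|---|---|---|
| a tenth | 0.7% v 2.3% | 2.93 | 0.1% v 0.7% | 2.96 |
| a quarter | 1.7% v 5.7% | 2.81 | 0.3% v 1.7% | 2.90 |
| half | 3.3% v 11.3% | 2.59 | 0.6% v 3.3% | 2.80 |
| all | 6.7% v 22.7% | 2.00 | 1.2% v 6.7% | 2.57 |

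**Power.** Simulated trials of 28 per arm (600 per scenario), with proper multiple imputation by arm, gave power of about 70% with 7% v 1% stopped, 67% with 11% v 3%, and 53% with 23% v 7%. In these runs 85% to 96% of imputed days fell before the day on which the child was known to be still unhealed. A likelihood that used the stop day as a lower bound recovered 2.99 to 3.07 days with 79% to 80% power on the same scenarios. This shows that the loss comes from ignoring the stop day. It does not show that simple censoring is the right treatment of a graft.

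**Equal healing, unequal grafting.** Both arms have mean 15 and C = 18 (z = 0.75). With g = 0.1, the mean is 15 − 0.1205/0.9773 = 14.88. With g = 0.5, it is 15 − 0.6023/0.8867 = 14.32. The false gap is 0.56 days, in favour of the arm that grafts more.

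**The case against.** The best reply is that the article never says a grafted child's healing day will be imputed. The Data storage section codes incomplete data as missing, unknown or not applicable, and a grafted child's date might take the last label. The imputation variables, which an article may leave to an analysis plan, could include serial wound area and percentage healed, burn depth and body surface area, all of which are collected. This has weight. With one assumed predictor correlated 0.8 with healing day, and all children unhealed at day 21 stopped, the estimate is about 2.5 days for 15 v 18 and 2.8 for 12 v 15. The bias is smaller but remains. The coding labels do not clearly exempt anyone from a rule worded to cover any missing data, and an analysis plan could exempt these children only by departing from that wording. Keeping data from before the stop supplies no healing day and does not say that the child is censored.

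It is also true that a generalised linear model can handle event times. The model family is therefore not the fault. The fault is the lack of any censoring or competing-event rule beside a universal imputation rule.

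Four stronger readings might be inferred, and the documents do not support them:
- **Every slow healer is imputed.** Dressing changes continue until healing or grafting, with no day-21 cut-off, so an ungrafted slow healer who stays on the assigned dressing has an observed day.
- **The difference will shrink to 2.0 days.** That needs about 7% v 23% stopped, arm-only imputation, and the historical 15 days as the faster arm. The stated hypothesis, that a silicone interface shortens healing, makes 12 v 15 at least as natural.
- **Excess grafting would go unseen.** Grafting is a secondary outcome and is compared between arms.
- **The 3–4-day visit spacing is a reason to change the model.** Simulated, it adds about 1.8 days of lag under a schedule common to all arms and raises the SD only from 4.0 to 4.1.

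**Conclusion.** The point holds in this form: the stated rules, read together, impute a healing day for children stopped by grafting, infection or dressing change, under an assumption that grafting in particular violates. The direction is clear when more slow healers are stopped in the slower arm: a true difference is understated. Unequal grafting can also produce a spurious advantage for the arm that grafts more.

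The size cannot be fixed from the article. It describes infection as very rare but gives no rate for grafting or switching. On the assumptions above, a true 3-day difference is estimated at about 2.9 days when few children are stopped, and at 2.0 to 2.6 days in the extreme case. If stops are rare, the bias is small. The case for changing the wording is that it concerns the outcome used to size the trial, the bias can run in a misleading direction, and the remedy is cheap.

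**What to change.** In the Data analysis section:
1. Analyse time from injury to re-epithelialisation with a time-to-event method. A complementary log-log model over visits is itself a generalised linear model, so the named model family and software can stay.
2. Treat grafting as a competing event, with a grafted child counted as not healed.
3. Censor children lost to follow-up at their last assessment.
4. State how children stopped for infection or dressing change enter the intention-to-treat analysis. One option is to censor them at the stop, with a sensitivity analysis because the stop may be informative.
5. Report the cumulative incidence of healing by arm, and the difference in median days or in restricted mean days to a horizon fixed in advance.
6. Limit multiple imputation to covariates and missed pain scores.

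The cost is analysis wording; no new data are needed. The downside is that the effect measure is no longer the mean difference behind the 28 per group. The text should relate the two and check power under the new model, which has not been calculated here.

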All participants in the study will have their dressings changed every 3–4 days at our burn centre as a standard measure. This protocol will be followed until full re-epithelialisation of the wound occurs or grafting of the wound is required [20]. After full re-epithelialisation occurs, participants will be followed up at 3 months and then 6 months to assess skin appearance and/or the presence of scarring.

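### The blanket multiple-imputation rule treats a right-censored healing day as wholly missing, so it can place healing before a visit at which the wound was seen open

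*Protocol article*

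**What the plan says.** In the protocol article, the Sample size section states: "The primary outcome measure will be days until wound re-epithelialisation". It plans on "Previous data in paediatric burn patients demonstrated re-epithelialisation within 15 (SD = 4) days" and says that "a minimally clinically important difference is 3 days". On loss it says: "Allowing for 20% loss to follow-up, a total of 100 participants will be required".

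The Data collection section brings every child back every 3-4 days, and "This protocol will be followed until full re-epithelialisation of the wound occurs or grafting of the wound is required". Under Days to re-epithelialisation, wound area and percentage healed are measured at each dressing change.

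The Data analysis section uses generalised linear models for primary and secondary outcomes, and adds: "Any missing data will be handled using the multiple imputation method". It names no censoring, no time-to-event method and no lower bound on an imputed healing day.

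**The concern.** A child lost before healing leaves two facts on file: the date of the last attended visit, and that the wound was still open then. The healing day is therefore right-censored at that visit. A rule that sends any missing value to multiple imputation treats the day as wholly unknown, so it may draw a value that the record disproves.

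Loss before healing can happen only while the wound is open, and slow healers have more visits at which to be lost. Even a constant dropout risk per visit therefore removes slower healers than those from whom values are imputed. Three things are at stake: arm means that read early, a diluted treatment difference with lower power, and a spurious difference if the arms lose children at different rates.

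The point concerns ordinary loss to follow-up only. Children whose data collection stops by rule (grafting, infection, change of dressing) raise a separate question, which is left aside here.

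**Working it through.** **Inputs from the document.** Mean 15 days, SD 4, difference 3 days, two-sided α 0.05, power 80%, 28 per group, 20% loss, total 100, visits every 3-4 days.

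**The plan's own figure.** n per group = 2(1.960 + 0.842)² × 4² / 3² = 27.9, so 28. This agrees with "Thus sample size was calculated at 28 per group at 80% power with an α of 0.05". For the total, 84 × 1.2 = 100.8 matches the stated 100; 84 / 0.8 would give 105. If 20 of 100 are lost, 80 / 3 = 26.7 per arm remain, and power is 78.2% (normal approximation).

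**One child.** Take T ~ N(15, 4²) and a child last seen open on day c. An unbounded draw falls at or before c with probability Φ((c − 15)/4). The expected true healing day is 15 + 4φ(z)/(1 − Φ(z)), with z = (c − 15)/4.

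| Last open visit | z | P(draw ≤ c) | Expected true day |
|---|---|---|---|
| Day 7 | −2.00 | 2% | 15.2 |
| Day 14 | −0.25 | 40% | 17.6 |
| Day 18 | 0.75 | 77% | 20.3 |

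The contradiction is rare for early loss and common for late loss, so the loss pattern decides the size.

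**Trial level: assumptions not in the document.** One pairwise comparison, N(15, 4²) v N(12, 4²); 33 per arm (equal allocation assumed); visits every 3.5 days; all loss before healing; 20 imputations from a normal model on arm alone, without a bound, combined by Rubin's rules. The comparator is a censored-normal likelihood that uses the fact that the wound was open at the last visit. Monte Carlo error is about 1 point.

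| Loss pattern | Lost | Imputed days before last open visit | Estimated difference, imputed (days) | Power, imputed | Power, censored |
|---|---|---|---|---|---|
| Unrelated to healing (two versions) | 20% | 10-11% | 3.0 | 75.2%, 75.3% | 77.8%, 78.9% |
| Mildly related to slow healing | 20% | 14% | 2.8 | 71.4% | 76.4% |
| Late in follow-up | 21% | 48% | 2.5 | 65.7% | 82.3% |
| Dropout time centred on day 18.4, SD 4 | 20% | 49% | 2.4 | 64.2% | 82.1% |
| Dropout time centred on day 21.0, SD 4 | 10% | 57% | 2.6 | 74.1% | 84.4% |

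The gaps are 2.6 and 3.6 points, 5.0 points, then 16.6, 17.9 and 10.3 points. When loss is unrelated to healing, most of the fall from about 85% (complete data) is the loss of data itself: complete cases give 76-77%.

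**Shift in arm means.** Imputation on arm alone reproduces the mean of the children seen to heal. In the mean-15 arm, a constant 5.5% dropout risk per visit (19% lost) puts that mean 0.25 days early. A risk of 2% per visit before day 12 and 12% after puts it 0.46 days early. Across such patterns the range is about 0.25-0.55 days.

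**Equal dressings.** In 1,000 null trials with equal loss, rejection was 4.8% with imputation and 5.3% with the censored analysis. With unequal loss and no true difference, 9% v 35% at constant risk gives a false difference of 0.42 days; 7% v 30% with late-weighted loss gives 0.77 days.

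**Does a Cox model recover the power?** In 1,500 trials under the two per-visit risks above (17% and 13% lost), the log-rank test, which is the Cox score test, had 70.9% and 76.5% power. Imputation had 72.5% and 77.5%, and censored-normal regression 79.0% and 85.1%.

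**The case against.** The strongest reply is that the imputation model used here is assumed. The article specifies neither predictors nor bounds, and such detail may sit in an analysis plan not shown. The trial records percentage re-epithelialised at every change, and burn depth; a model using these would produce fewer contradicted dates. This stands, and it lowers the magnitudes. It does not remove the point, which rests on the stated rule: that rule covers the healing day without exception and requires neither bound nor interim data.

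Several stronger readings are tempting but unsupported:

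- **A fixed power loss.** The two per-visit dropout risks give 6-8 points, and a reader might take that as the cost. The document gives neither the timing of loss nor its relation to healing, so only a range can be defended.
- **All 20% lost before healing.** Follow-up runs to 6 months after healing, while healing is expected at about 15 days. The document does not say when the loss occurs. With less loss before healing, every figure above falls.
- **The 77% as typical.** It applies to one late last visit and a draw that ignores covariates.
- **False positives.** Type I error is intact with equal loss. Nothing in the document predicts loss as unequal as 9% v 35%. Incomplete blinding makes differential loss conceivable, no more.
- **Slow healers are the ones lost.** Families may also stop attending when a wound is nearly closed. Censoring would then be informative and a censored analysis would be biased too.

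**Conclusion.** The concern holds as a fault in a stated rule. As written, it allows the primary outcome to contain healing days that the trial's own visits disprove. On the assumptions shown (all loss before healing, 10-20% lost, imputation by arm without bound or interim healing data), about 10-57% of imputed days are contradicted. Power is 3-5 points below a censored regression when loss is unrelated or mildly related to healing, and 10-18 points below when it is late or concentrated in slow healers. In those latter cases the 3-day difference also shrinks to about 2.4-2.6 days. Arm means read about 0.25-0.55 days early under the per-visit dropout risks tried, which is modest against a 3-day important difference. Markedly unequal loss could create a false difference of about 0.4-0.8 days. The change should be made because it is nearly free, not because the trial would otherwise fail.

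**What to change.** In the Data analysis section, exempt days to re-epithelialisation from unbounded imputation. State that a child lost while unhealed is right-censored at the last visit with an open wound. Compare the arms with a censored regression, for example normal, which keeps the result as a difference in days. If multiple imputation is kept for this outcome, require every drawn healing day to be later than that child's last open visit, preferably with the recorded percentage healed as a predictor. Keep multiple imputation for data that are truly unobserved, such as missed pain scores.

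A Cox model would also avoid contradicted dates, but it should not be presented as recovering power under the planning assumptions, and it gives a hazard ratio rather than days.

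The cost is wording only, since visit dates and wound status are already recorded. The downside is that censored regression relies on a distributional assumption and on loss being non-informative given the data. Add a sensitivity analysis that varies both, including the case in which children leave when nearly healed.
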